##### The impact of family environment and parenting patterns on brain development

Regarding the secondary research results, we will conduct a comprehensive analysis from two aspects: the exposure of adverse factors in mothers during pregnancy and the family environment and parenting patterns after birth. For maternal exposure to adverse factors during pregnancy, on the one hand, regarding the correlation between inflammatory indicators and brain development, we will conduct correlation analysis between brain indicators such as MRI-derived brain volume, cortical thickness, and EEG power spectral density, and the levels of inflammatory cytokines such as C-reactive protein (CRP) and Interleukin-6 (IL-6). Group children according to the inflammatory levels and compare their brain imaging, electrophysiological data, and scores of relevant abilities of children. On the other hand, for other adverse conditions during pregnancy, conduct regression analysis to explore the potential links with the future development of children. In the analysis of family factors after birth, first conduct correlation and regression analysis between the scores of the quantified family parenting scale and brain indicators such as MRI-derived brain volume, cortical thickness, and EEG power spectral density. At the same time, explore the pathways through which parenting patterns affect children's intellectual development through mediation analysis. In addition, associate family environment variables with children's emotional regulation indicators, and compare the differences in children's cognitive development under different parenting styles.

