## Methods and analysis

### Research subject

The study subjects were infants and children aged 0–3 years and their mothers, and the Xiamen Children's Brain Development Cohort recruited the study subjects from the society (kindergartens, elementary schools, and other institutions) and the neonatal department of Xiamen Children's Hospital. Based on the information of the mothers' pregnancy—related medical history, infants whose mothers had high inflammatory indices during pregnancy (e.g., CRP, interleukin−1β, interleukin−6, interleukin−10, and macrophage inflammatory factor−1β), or had chorioamnionitis, pathologic abnormalities of the placenta, preterm premature rupture of the membranes, or had combined gestational hypertension and diabetes mellitus with maternal inflammatory diseases were included in the observation group. Infants without maternal inflammation were the control group.

Characteristics of our included subjects included:(1) age 0–3 years;(2) gestational age 37–42 weeks;(3) birth weight >2.5 kg; and(4) no significant birth complications. Characteristics of excluded subjects included:(1) history of resuscitation from asphyxia at birth;(2) congenital structural anomalies;(3) presence of inborn inherited metabolic disorders such as phenylketonuria, galactosemia, and congenital hypothyroidism;(4) presence of a major medical condition affecting growth, or development; and(5) contraindications to magnetic resonance imaging (MRI).

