#### Sample size

The formula for calculating the sample size is based on the comparison of the average values of the two independent samples:

$$\begin{array}{l} N\;=\;\frac{{2\left(Z_{\alpha }+Z_{\beta }\right)}^{2}\sigma^{2}}{d^{2}} \end{array}$$

Where σ is the estimated standard deviation, *d* represents the difference between the two sample means, and *Z*_α_ and *Z*_β_ are the quantiles of the standard normal distribution corresponding to α and β, respectively. A previous Greek study using the McCarthy Scales for Children's Abilities to measure children's brain development found that the difference between the memory scores of children born to mothers with a hyperinflammatory state during pregnancy and those born to normal mothers was −4.4 (−8.3, −0.5) (18). Substituting σ = 0.05 and β = 0.2 gives *N* = 1603, based on a 1:1 calculation of mothers in the inflammatory group vs. the normal group, a total of 2*N* = 3206 pregnant women needed to be included in the entire study.

Hospital clinicians and nurses explained the objectives of the study, the process, the potential benefits of participation, and the confidentiality of the study to all families eligible for inclusion. All investigators entering the cohort signed an informed consent form. The Xiamen Child Brain Development Cohort provided each mother and child pair with a unique family ID for further follow-up. Participants could withdraw from the cohort at any time. The study was approved by the Clinical Ethics Committee of Xiamen Children's Hospital and the participating hospitals.

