#### Genetic and exposome testing

At the time of enrollment, 2 ml of blood from each parent and child were drawn once, whole exome sequencing and exposome were performed, and multivariate statistical methods were used to analyze genes and biomarkers related to brain, early language and emotional development. In addition, through the deep sequencing of the whole genome, a variety of genetic analysis methods, including candidate-gene analysis, whole-gene analysis, and multi-gene risk combination analysis methods, will be used to explore the molecular mechanisms of brain structure, function, connections, and the developmental trajectory of language and emotion, and elucidate the precise mechanism of gene expression during human brain development.

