##### Gene-environment interaction

In the data analysis of gene–environment interactions, this study will be base on whole exome sequencing data. First, variant detection and quality control will be performed using the Genome Analysis Toolkit (GATK). ANNOVAR will be utilized for functional annotation of the variants, and high-quality loci will be screened through the Hardy-Weinberg Equilibrium (HWE) test. We will focus on the variants of candidate genes related to brain development and loss-of-function mutations. Subsequently, the Sequence Kernel Association Test with Optimal weighting (SKAT-O) will be employed to analyze the association between gene sets and brain development phenotypes. Meanwhile, a generalized linear model will be constructed, incorporating pregnancy inflammation indicators (such as CRP and IL-6 levels), environmental exposure variables, and their interaction terms with gene variants to test the gene–environment interaction effects. By referring to the literature in fields such as neural synapse development and inflammatory signaling pathways, genes with significant effects in the interaction will be screened out. For the screened genes, methods such as metabolomics and proteomics will be further used to verify their regulatory mechanisms in brain development, analyze the impact of genes on the early-life brain structure and function of infants, and ultimately reveal the molecular pathways through which the interaction of genes, pregnancy inflammation, and environmental exposure affects early brain development. It is expected to identify at least 10 key genes with significant effects and clarify their potential biological mechanisms.

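### The inflammatory-versus-normal comparison on which the study was sized appears in no described analysis, and the level-based grouping used instead can put mothers exposed by diagnosis alone in the reference group

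*Protocol article*

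**What the plan says.** **Who is exposed.** Under Research subject, the observation group takes in "infants whose mothers had high inflammatory indices during pregnancy", with CRP and several cytokines as examples. By an alternative route it takes in mothers who "or had chorioamnionitis, pathologic abnormalities of the placenta, preterm premature rupture of the membranes", or who had hypertension and diabetes together with inflammatory disease. Either route is enough. The comparator is stated as "Infants without maternal inflammation were the control group".

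**What the study is sized on.** The Sample size section arrives at 1603 per group, "based on a 1:1 calculation of mothers in the inflammatory group vs. the normal group".

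**What is analysed.**
- The Data analysis section on family environment and parenting, which also covers pregnancy exposures, correlates CRP and IL-6 levels with brain measures. It then says: "Group children according to the inflammatory levels and compare their brain imaging, electrophysiological data, and scores of relevant abilities of children". Other adverse pregnancy conditions go to a separate regression.
- The secondary-outcome plan on maternal adverse factors makes the same split. It names chorioamnionitis, placental pathology, gestational diabetes and gestational hypertension on the side that is not inflammation level.
- The gene-environment model, which serves a primary outcome, is described as "incorporating pregnancy inflammation indicators (such as CRP and IL-6 levels), environmental exposure variables" plus interaction terms with gene variants.
- The deep-learning model takes pregnancy inflammatory indicators as its input.

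**The concern.** The article uses two definitions of maternal inflammation. In the design, a diagnosis such as chorioamnionitis is sufficient for exposure. In the secondary outcomes and their analysis, the same diagnosis is set apart from inflammation and studied as something else.

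Two things follow. The two-group comparison that justifies the sample size is not among the analyses described. And a mother who counts as exposed by diagnosis, but whose markers were measured and not raised, belongs in the low-level group when children are regrouped by level. If her condition affects the child's brain development, the reference group is contaminated and the difference shrinks. Two printed definitions also leave the choice of exposure open until the data have been seen.

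**Working it through.** **The definitions side by side**

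| Section | Exposure used | Where chorioamnionitis and placental pathology fall |
|---|---|---|
| Research subject | Raised marker or diagnosis | Inside inflammation |
| Sample size | Inflammatory vs normal, 1:1 | Inside, if the groups are those of Research subject |
| Secondary outcome, maternal adverse factors | Inflammatory level | Outside, as other conditions |
| Data analysis, risk model | Inflammatory indicators | Not named |
| Data analysis, gene-environment | Indicators such as CRP and IL-6 levels | Not named; may enter as environmental exposures |
| Data analysis, secondary results | CRP/IL-6 level and level groups | Not named; other conditions have a separate regression |

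The remaining group comparison, under Cohort and data objectives, concerns baseline subgroups such as gender and gestational age. No row of the analysis compares observation with control.

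One could read inflammatory level loosely, as observation versus control. The secondary-outcome text does not allow this, because it places two of the diagnoses that define the observation group on the other side of the split.

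**The plan's own figure.** The formula is N = 2(Zα + Zβ)²σ²/d², with d = 4.4 and β = 0.2.
- With σ = 0.05 as printed and a two-sided 5% level: 2 × (1.960 + 0.842)² × 0.0025 / 19.36 = 0.002, which rounds up to 1 per group.
- If 0.05 was meant as α, no standard deviation is stated. N = 1603 then needs σ = 4.4 × √(1603 / (2 × 7.849)) = 44.5.

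So 1603 cannot be reproduced from the stated inputs. That is a separate problem, and the illustration below does not depend on σ.

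**Illustration of the dilution.** Assumptions: equal groups of N, 80% power at two-sided 5%, and a fraction f of the exposed group exposed by diagnosis alone. Those mothers carry the full effect d and are moved to the low-level group.
- Group sizes become (1 − f)N and (1 + f)N.
- The low-level group contains a share f/(1 + f) of exposed mothers, so the expected difference is d/(1 + f).
- The standard error is σ√(2 / (N(1 − f²))).
- The expected test statistic falls from 2.802 to 2.802 × √((1 − f)/(1 + f)), and σ cancels.
- Power = Φ(that value − 1.960). The sample size for equal power rises by (1 + f)/(1 − f).

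| f (assumed) | Difference, from 4.4 | Power | N multiplier |
|---|---|---|---|
| 0 | 4.40 | 80% | 1.00 |
| 10% | 4.00 | 72% | 1.22 |
| 20% | 3.67 | 63% | 1.50 |
| 50% | 2.93 | 37% | 3.00 |

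Table 4 does not supply f. It gives no split into marker only, diagnosis only and both. Its 47 ruptures of membranes are not limited to preterm cases, and it does not say that its 187 mothers with inflammation are the observation group of Research subject.

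**The case against.** The best defence is that a marker-level contrast asks a different question. A mother without raised markers is correctly low on that scale, and the effect size borrowed for the sample size concerns a hyperinflammatory state, arguably nearer to a marker contrast than to a composite. Much of this stands. The analysis by level is legitimate, and dilution arises only to the extent that the diagnoses themselves affect the child. That the sized groups are the composite ones is an inference, though a strong one, since Research subject is the only place where the two groups are defined.

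It is also fair that this is a condensed article. Cut-offs for level and the handling of untested mothers may sit in a fuller document. The conflict between the printed sections is not a matter of omitted detail.

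Three stronger readings are tempting and not supported:
- **That diagnosis-only mothers are lost from the analysis.** Other conditions have their own regression. Cohort and data objectives counts pregnancy complications among the environmental data, so they may enter the gene-environment model as environmental exposures.
- **That pregnancy markers must be missing because "At the time of enrollment, 2 ml of blood from each parent and child were drawn once".** That sample serves sequencing and exposome testing. Pregnancy exposure comes from questionnaires and medical records.
- **That Table 4 fixes the size of the bias.** For the reasons given with the illustration, it does not.

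**Conclusion.** The point holds as a conflict of definitions with a consequence for the analysis. Research subject counts certain diagnoses as maternal inflammation, while the secondary outcomes and their analysis count at least chorioamnionitis and placental pathology as something else. The comparison that the study was sized on is not among the analyses described. As written, a mother exposed by diagnosis alone can sit in the low-level reference group of the inflammation comparison.

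The resulting dilution is possible but of unknown size. The power range of 72% down to 37% rests on assumed diagnosis-only shares of 10% to 50% and on an equal effect for those mothers, neither of which the article states. A smaller effect in them would mean less dilution of the level contrast, and would make the composite the more diluted of the two. The change should be made, but nothing here shows that the existing marker analyses are invalid for their own question.

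**What to change.** 1. In the Data analysis section that covers pregnancy exposures, add the comparison of observation with control group, as defined under Research subject, as the main inflammation group contrast. It is the one the study was sized on.
2. Keep CRP and IL-6 level as a separately labelled dose-response analysis among mothers with a recorded pregnancy value, and state how many contribute. Use only controls without a qualifying diagnosis as its low-level reference group.
3. In the gene-environment model, state whether the inflammation term is the composite group or the marker level, and report the other as a sensitivity analysis.
4. Reconcile Research subject with the secondary-outcome text on whether the diagnoses count as inflammation.

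This changes wording and adds one comparison; no new data are needed. There are two costs. The composite is less specific than a marker level, which is why the marker analysis stays. And a mother with neither a marker test nor a diagnosis is a control only by default, so the number of such mothers should be reported.

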##### Research plan on the impact of maternal adverse factor exposure during pregnancy on infant early brain development

Focusing on maternal exposure to inflammation during pregnancy, this plan aims to analyze its mechanism of action on infant early brain development. On the one hand, we will study the correlation between the changes in inflammatory indicators during pregnancy and infant brain development. By comparing the brain imaging and electrophysiological data of children under different inflammatory levels, as well as the development of children's intelligence, cognitive ability, motor ability and other abilities, we will explore the potential impact of maternal inflammation during pregnancy on the development of brain structure and function. On the other hand, regarding other adverse conditions during pregnancy, such as chorioamnionitis, placental pathological abnormalities, gestational diabetes mellitus, gestational hypertension and other pregnancy-related diseases, as well as adverse environmental exposure during pregnancy, we will analyze their impacts on the structure and function of infant brains, and the potential links between such impacts and the future development of infants in terms of intelligence, cognition, emotion, and motor skills.

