##### Construction of infant brain development models

Integrate the volumes of MRI brain regions, time-frequency features of EEG, inflammatory indicators during pregnancy, and questionnaire scores of children in different ability areas. Reduce the dimensionality through principal component analysis to generate multimodal feature vectors and input them into a Transformer to construct a deep learning model. Train the model using cross-validation and prevent overfitting through the Dropout method and the AdamW optimizer. Take the AUC as the core index, and simultaneously calculate the sensitivity, specificity, accuracy, and other indicators of the model. Verify the generalization ability of the model using an international public database, and locate the key predictive factors through the SHapley Additive exPlanations (SHAP) values and the Local Interpretable Model-agnostic Explanations (LIME) algorithm. Combine the anatomical localization of brain regions to explain the risk prediction mechanism of how inflammation during pregnancy affects brain development, and ensure the clinical application value of the model.

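### Child ability scores are related to maternal marker levels only by comparing groups; adding a regression on uncut CRP/IL-6 would cheaply recover information if the relation is roughly linear

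*Protocol article*

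**What the plan says.** The relevant text is in the protocol article, Data analysis, in the subsection on family environment and parenting patterns, which also covers maternal exposures. It names two analyses of pregnancy inflammation.

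- The first uses the uncut scale: "we will conduct correlation analysis between brain indicators such as MRI-derived brain volume, cortical thickness, and EEG power spectral density" are correlated with "the levels of inflammatory cytokines such as C-reactive protein (CRP) and Interleukin-6 (IL-6"). The outcomes listed are brain measures.
- The second uses groups: "Group children according to the inflammatory levels and compare their brain imaging, electrophysiological data, and scores of relevant abilities of children". Ability scores appear here and not in the first analysis.

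The matching aim under Secondary outcome is also worded as a comparison: "By comparing the brain imaging and electrophysiological data of children under different inflammatory levels, as well as the development of children's intelligence", followed by cognitive and motor ability.

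Two other subsections of Data analysis use the markers with no grouping stated. The gene-environment model is described as "incorporating pregnancy inflammation indicators (such as CRP and IL-6 levels), environmental exposure variables, and their interaction terms with gene variants", and the prediction model takes in "inflammatory indicators during pregnancy, and questionnaire scores of children in different ability areas".

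**The concern.** CRP and IL-6 are measured quantities, and the ability scores are numerical and are to be converted to Z-scores. Comparing groups treats mothers just either side of a cut as different and all mothers within a group as alike. No dose-response slope is then estimated for ability, although the same paragraph uses the full scale for brain measures.

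The two sets of results would also rest on different exposure scales. A positive correlation with brain volume beside a null grouped result for ability could reflect the weaker method and not a real difference between the outcomes.

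**Working it through.** **Does another section fill the gap?** The gene-environment model tests interaction between genes and marker levels, and its outcome is not named as an ability score. The prediction model is judged by AUC and is not an association analysis. Neither supplies an inflammation-ability association on the uncut scale.

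**The plan's own power figure.** No power is stated for either analysis of marker levels. The only figure is under Sample size: β = 0.2 for a comparison of two independent means, with a difference of 4.4 on a memory score and N = 1603 per group. That N cannot be reproduced. With σ = 0.05 as printed, 2 × (1.960 + 0.842)² × 0.05² / 4.4² = 0.002. If 0.05 was meant as α, no SD is given, and N = 1603 implies an SD of about 44.5 (two-sided). This is a separate matter. The only input used below is 80% power at two-sided α = 0.05, where the two-sidedness is an assumption.

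**Further assumptions, not in the document.** The effect is linear in the log marker, and the log marker is roughly normal.

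**Formulas.** For one cut with share f above it, relative efficiency is E = φ(c)² / [f(1 − f)]. For k equal groups with a trend test, E is the average of the squared group means of a standard normal variable. With δ = 1.960 + 0.842 = 2.802, the power of the grouped analysis is Φ(δ√E − 1.960) when the continuous one has 80%. In the other direction, the continuous analysis has Φ(δ/√E − 1.960) when the grouped one has 80%.

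| Grouped analysis | E | Its power if continuous has 80% | Points lost |
|---|---|---|---|
| Median split | 0.637 | 61% | 19 |
| Top quarter against rest | 0.539 | 54% | 26 |
| 80/20 cut | 0.490 | 50% | 30 |
| Tertiles, trend test | 0.793 | 70% | 10 |
| Quartiles, trend test | 0.861 | 74% | 6 |
| Tertiles, 2-df omnibus test | 0.793 | 60% | 20 |

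Median split worked through: Φ(2.802 × 0.798 − 1.960) = Φ(0.275) = 0.61. In reverse: Φ(2.802 / 0.798 − 1.960) = Φ(1.55) = 0.94. Starting instead from 80% for a tertile or quartile trend test, the continuous analysis has about 88% or 86%. A 90/10 cut, more extreme than those tabled, would fall to 37%.

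**Dependence on effect size and sample size** (median split; continuous power, then grouped power):

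- At 3,206 children: r = 0.03, 40% and 27%; r = 0.05, 81% and 62%; r = 0.08, 99.5% and 95%; r = 0.10, nearly 100% and 99.5%.
- At the 360 pairs reported under Preliminary results: r = 0.05, 16% and 12%; r = 0.10, 47% and 33%; r = 0.15, 82% and 62%; r = 0.20, 97% and 86%.

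**Where the advantage shrinks or reverses.** With 1,603 per group, a difference of 4.4 and an assumed SD of 15 to 25, two-group power is at least 99.8%, so nothing material is lost. If the true effect is a step at the median cut, a grouped analysis with 80% power corresponds to about 61% for the continuous one.

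**Why the scale matters.** If the effect is linear in the log marker and the log marker has SD 1 (assumed), the raw level correlates 0.76 with its log. A Pearson correlation on the raw level then has about 57% power where the log-scale analysis has 80%.

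**The case against.** The strongest reply is that a group contrast is what this study was designed for. Under Research subject, observation and control groups are defined partly by diagnoses with no continuous scale, such as chorioamnionitis. Sample size is based on a two-mean comparison of an ability score, and 187 of the first 360 mothers (51.9%) had inflammation. This stands for the observation-versus-control contrast, which should not be demoted. It does not cover the text at issue, which groups by marker level.

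Other points that stand in part:

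- Recruitment by exposure status may give a marker distribution far from normal. If the values cluster in two groups, a cut between them costs less than the 0.64 efficiency suggests.
- The article does not say that every mother, controls included, has a measured CRP or IL-6.
- The list of brain indicators is illustrative, and the analysis is secondary and exploratory. Even so, ability scores are named separately and assigned to the grouped step.
- Cut-points and transformations may be fixed in a fuller plan that is not shown. Their absence is no part of this point.

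A reader might infer that the ability question loses about 20 points of power for nothing. The documents do not support that. The figure needs a median split (or a three-group omnibus test), which is not stated, and a continuous analysis that starts at 80%. The plan's 80% belongs to a two-group ability comparison. Carried over to a median split on marker level, it implies a forgone gain of about 14 points (80% to 94%), not a fall to 61%.

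**Conclusion.** The point holds in a limited form. Within the plan's analysis of measured inflammatory levels, ability scores are handled only by comparing groups, while uncut levels are correlated only with brain indicators. This is a stated choice of a method that is weaker under a roughly linear relation, and not merely missing detail.

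The size is conditional: about 0 to 30 points of power for cuts no more extreme than 80/20, depending on the cuts, the effect and the number of children. It rests on a linear effect in a roughly normal log marker, and it reverses for a step at the cut. It would be wrong to conclude that the continuous scale is abandoned throughout the plan or that grouping has no purpose. This is a cheap improvement to a secondary analysis; it does not invalidate the design.

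**What to change.** In the Data analysis subsection that covers maternal exposures, add a regression of each ability Z-score on the continuous CRP or IL-6 level, for example log-transformed, with a spline or quadratic term to check for non-linearity. Make it the main analysis of the measured marker levels, among children whose mothers have measured values. Keep the comparison by marker-level group as a supporting display with cuts set in advance; together with the non-linearity check, this guards against a threshold effect being missed. Leave the observation-versus-control contrast of Research subject and Sample size unchanged.

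The cost is one or two sentences and no new measurements. A handling rule is needed for values below the assay limit and for mothers without a measured marker, and a slope is slightly less simple to present than group means.
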